### Outcome measures

This is a long-term follow up of lung function and cardiac outcomes in a group of extremely prematurely born adults who have had exposure to antenatal steroids and postnatal surfactant.

Our primary outcome is FEV_1_/FVC in extremely prematurely born adults with postnatal corticosteroid exposure versus no postnatal corticosteroid exposure.

Our secondary outcomes will include spirometric lung function, cardiopulmonary exercise test of maximum oxygen uptake (VO_2_) and PAP estimation by cardiac ultrasound of UKOS participants compared to term born controls.

We will also compare these primary and secondary outcomes in participants enrolled in the UKOS trial as per their initial designation of mode of ventilation.

### Sample size

The generally accepted lung function threshold for developing symptoms in COPD is a FEV_1_/FVC ratio below 70% of the predicted value^42^ which corresponds to a z-score of −2.19. The dexamethasone exposed group of the UKOS cohort had an FEV_1_/FVC ratio z-score of −1.83 which is above the threshold, but very close to it.^11^ In contrast the corticosteroid unexposed group had an FEV_1_/FVC ratio z-score of −0.89. The cohort was assessed at 16–19 years of age and are now ~8 years older and possibly symptomatic. Calculations have been based on the FEV_1_/FVC ratio, as it has been associated with a clinical symptom threshold.^43^ To detect a clinically significant difference in FEV_1_/FVC of 0.33 between the steroid and non steroid exposed (the difference in the mean FEV_1_/FVC z-score between the results of the 11–14 year olds and 16–19 year olds in the UKOS cohort) with a SD of the FEV_1_/FVC z-score of 1.21 and with 90% power and 5% significance, we will need 64 patients per group—128 in total. We will aim to recruit 150 patients from the UKOS cohort to allow for drop out.

To detect a clinically significant difference in the mean PAP of 2.31 mmHg as previously observed between children born preterm versus children born at term when they were 11–14 years of age with a SD of the mean PAP of 2.8 mmHg^16^ and with 90% power and 0.01 significance, we will need 44 patients per group (44 controls and 44 prematurely born young people). We will aim to recruit 50 term-born controls to allow for drop out.

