Despite the well reported risks of corticosteroids, our recent survey demonstrated that 100% of tertiary units are still prescribing systemically administered corticosteroids.^12^ It is therefore important to determine if lung function in adulthood has deteriorated further in those exposed to corticosteroids in the neonatal period as compared to those unexposed. This would emphasise that prescribing practices and administration of postnatal corticosteroids should be reviewed.

Preterm infants have altered immune regulation and are at risk of sustained inflammation.^13^ They are also at risk of dysbiosis, an alteration in the composition or diversity of their microbiome, which can result in invasion of virulent species and immune disruptions.^14^ The potential link between airway dysbiosis, sustained inflammation and long-term outcome has not been evaluated in extremely prematurely born adults^14^ and is one of our aims.

BPD is often associated with pulmonary vascular disease and secondary PH. A case control study from the Swedish pulmonary arterial hypertension registry demonstrated that premature birth was associated with a three-fold increased risk for adult PH.^15^ We showed in the UKOS cohort, nearly half of 193 adolescents with a mean gestational age at birth of 27 weeks had a mean pulmonary artery pressure (PAP) greater than 20 mmHg when aged 11 to 14 years of age.^16^ The presence of PH and its contribution to worse lung and heart function requires investigation, especially in the context of growing evidence of abnormal cardiac morphology in individuals born prematurely.

Individuals born preterm have been shown to have unique cardiac phenotypes with altered morphology and functional capacity in childhood and adolescence with evidence of increased risk of early cardiovascular disease.^17,18^ The UKOS cohort offers a unique opportunity to characterise these unique cardiac features in a large number of adults born extremely prematurely in the modern era of neonatal care.

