### Statistical analysis

For the main analysis of outcomes, we will use mixed models, with the mother or the pregnancy as the random effect to allow for clustering due to multiple births. Skewed lung-function outcome data will be log-transformed.

All study outcome analyses will be adjusted for observed baseline imbalances between groups by incorporating the unbalanced factors as fixed effects in the multifactorial model. Sensitivity analyses will be conducted to explore the robustness of adjustment for baseline imbalances between groups. Propensity score matching, used in the follow up of UKOS patients when aged 16–19,^44^ will be utilised as part of the sensitivity analysis methodology. Unadjusted and adjusted analyses will be presented to show the effects of adjustment as estimates with 95% confidence intervals. As we have a clearly predefined single primary outcome, FEV_1_/FVC, we will not adjust for multiple testing of the secondary outcomes. Neonatal baseline data will be compared for the children recruited and not recruited at age 24–28 years to determine the representativeness of the group with follow-up data. Those variables that differ between recruited versus not recruited will be further adjusted for a sensitivity analysis. Some participants will be unable to complete all tests and, so, multiple imputation using chained equations will be used to impute missing data.

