## Discussion

Longitudinal follow up of children and adolescents born preterm has provided evidence of adverse cardiopulmonary outcomes^9,45^ including abnormal lung function, increased risk of asthma, COPD, PH and abnormal cardiac morphology and function with reduced exercise tolerance.^46,47^ Many of these outcomes were reported in cohorts that were born in a period prior to widespread use of surfactant and antenatal corticosteroids.

The importance of the continued follow up of the UKOS cohort as they now reach adulthood, is emphasised by the previous findings of reduced lung function and a trend towards spirometric parameters consistent with a diagnosis of early COPD when they were adolescents, in particular in individuals exposed to corticosteroids in the neonatal period.^11^ In addition, the UKOS cohort were born in the “modern” era of neonatology with more than 90% exposed to surfactant and antenatal corticosteroids.^48^ Whether there has been a further deterioration in lung function meeting spirometry or clinical criteria for early COPD, particularly in those with postnatal corticosteroid exposure needs urgent testing.

While the focus of primary and secondary outcomes is on airway abnormalities as measured by spirometry, our methodology includes other important measurements of lung function (DL_CO_, Fe_NO_, LCI) which will provide evidence of long-term pulmonary gas exchange, airway inflammation and ventilation inhomogeneity.^49^ In addition, prematurity has been shown to affect respiratory muscle function with prematurely born infants having decreased maximal expiratory pressures,^50^ but it is not known whether the effect of prematurity persists to adulthood. This study will establish the respiratory muscle reserves of prematurely born adult individuals which is important as they are thought to present with early COPD.^51^

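### The 0.33 target for the steroid comparison is a cohort change between two ages, and the single-age primary test cannot show further deterioration in the exposed

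*Protocol article*

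**What the plan says.** The protocol article, under Sample size, sets the target for the primary comparison: "To detect a clinically significant difference in FEV_1_/FVC of 0.33 between the steroid and non steroid exposed". In parentheses it explains where 0.33 comes from: "the difference in the mean FEV_1_/FVC z-score between the results of the 11–14 year olds and 16–19 year olds in the UKOS cohort". The other inputs follow ("with a SD of the FEV_1_/FVC z-score of 1.21 and with 90% power and 5% significance"), and then the result: "we will need 64 patients per group—128 in total".

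The same section reports the exposure groups at 16–19 years. The dexamethasone-exposed group had a mean z-score of −1.83. "In contrast the corticosteroid unexposed group had an FEV_1_/FVC ratio z-score of −0.89".

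The Introduction says that it is important to "determine if lung function in adulthood has deteriorated further in those exposed to corticosteroids in the neonatal period as compared to those unexposed". The Discussion returns to this: "Whether there has been a further deterioration in lung function" has occurred, particularly in those with steroid exposure, is said to need urgent testing.

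Under Outcome measures, the primary outcome is FEV1/FVC in exposed versus unexposed adults born extremely preterm, who are now 24–28 years old. Under Statistical analysis, outcomes are analysed with "mixed models, with the mother or the pregnancy as the random effect", adjusted for observed baseline imbalances. The formal hypothesis, at the end of the Introduction, is that exposed adults will have poorer lung function than unexposed adults.

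**The concern.** There are two linked problems.

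First, the target is labelled as one quantity and derived from another. A shift in the cohort mean between two ages says nothing about how far apart the exposed and unexposed groups are, or how far apart they would have to be to matter. The between-group figure that the section does contain is nearly three times as large.

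Second, the motivating question is about change and the primary test is about level. The groups were already well apart at 16–19 years. A difference at 24–28 years could be the old gap carried forward, a smaller gap after partial catch-up, or a larger gap after further decline. A comparison at one age does not separate these. At stake is the reading of a positive result: it could be taken as evidence that steroid-exposed adults are still losing ground, and the Introduction ties that question to a review of prescribing practice.

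**Working it through.** **Inputs.** From Sample size: target 0.33, SD 1.21, 90% power, 5% significance (taken as two-sided), 64 per group, group means −1.83 and −0.89 at 16–19 years. Equal groups are implied by the per-group figure; the actual split is not given.

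**The plan's own figure.** Two-group formula: n per group = 2 × SD² × (z₀.₉₇₅ + z₀.₉₀)² / d².
- With d = 0.33 and SD = 1.21: 2 × 1.4641 × (1.960 + 1.282)² / 0.1089 = 282.5, so 283 per group. The stated 64 is not reproduced. One-sided, 80% power and paired variants do not give it either. This is a separate error and the present point does not depend on it.
- The same formula with the 0.01 level reproduces the pulmonary artery pressure figure: 2 × 2.8² × (2.576 + 1.282)² / 2.31² = 43.7, so 44 per group, as stated.

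**The observed between-group gap.** −0.89 − (−1.83) = 0.94, and 0.94 / 0.33 = 2.8.

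**What the single-age test shows if nothing has changed.** Standard error at 64 per group = 1.21 × √(2/64) = 0.214. If the gap is still 0.94, the expected test statistic is 0.94 / 0.214 = 4.4. Power from the noncentral t distribution, 126 degrees of freedom, two-sided 5%:

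| True gap at 24–28 years | Power, 64 per group |
|---|---|
| 0.94 (unchanged) | 99% |
| 0.70 | 90% |
| 0.61 (0.94 − 0.33) | 81% |
| 0.47 (half of 0.94) | 59% |
| 0.33 | 33% |

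With unequal groups, assuming 20% to 25% exposed among 128 (25 versus 103, or 32 versus 96), a gap of 0.94 gives 93% to 97%.

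**A difference in change, for illustration only.** With SD 1.21 at both ages and correlation ρ between them, the SD of change is 1.21 × √(2(1 − ρ)). The documents do not give ρ. For a between-group difference in change of 0.33 with 64 per group:

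| Assumed ρ | SD of change | Power |
|---|---|---|
| 0.5 | 1.210 | 33% |
| 0.6 | 1.082 | 40% |
| 0.7 | 0.937 | 51% |
| 0.8 | 0.765 | 68% |
| 0.9 | 0.541 | 93% |

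This assumes that every participant has a 16–19-year value. The Recruitment section draws from the UKOS database, not only from those seen at that age, so fewer may have one. The value 0.33 is used here only to show the scale; no document makes it a target for this quantity.

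**The case against.** The formal hypothesis is a difference in level, and the primary outcome tests exactly that. The sample size rationale is also partly about level, since it discusses distance from a threshold z-score of −2.19, and the Discussion speaks of deterioration that meets criteria for early COPD. This stands: the primary outcome is not wrong for its hypothesis. The mismatch is with the Introduction's question about further deterioration relative to the unexposed, with its counterpart in the Discussion, and with the source of the 0.33.

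The 99% figure needs the whole 0.94 gap to survive. The analyses will be adjusted for imbalances, and the article does not say whether −1.83 and −0.89 are adjusted. The −1.83 is for dexamethasone exposure, whereas the primary contrast is any postnatal corticosteroid. This also stands, and it is why 81% and 59% are shown beside the 99%. A reader might infer that the primary result is a foregone conclusion; the documents do not support that.

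A longitudinal analysis may be planned in a fuller document. The article describes no participant effect, age term or earlier FEV1/FVC value, and mentions comparison with the 16–19-year results only for the shuttle sprint test. Silence in a condensed article is not proof of absence, so the point rests on what the stated primary comparison can show.

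A reader might also infer that 0.33 is the right target once moved to a steroid-by-age term. That would repeat the error: 0.33 is a change in the cohort mean, not a difference in change between exposure groups.

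**Conclusion.** The point holds in this form. The article describes 0.33 as a between-group difference when by its own definition it is a change between two ages; the between-group figure that it reports is 0.94. The primary comparison suits the level hypothesis but does not bear on further deterioration in the exposed. With no further deterioration at all, it would be positive with about 99% probability if the 0.94 gap persists, 81% if the gap is 0.61 and 59% if it is 0.47. These figures assume SD 1.21, 64 per group in equal groups, a two-sided 5% test and no design effect from multiple births.

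**What to change.** 1. Keep the cross-sectional primary outcome. Stop describing 0.33 as a difference between exposed and unexposed. State the target as a between-group difference, with a reason why that size matters, and report the power that 64 per group gives: 90% for about 0.70, 33% for 0.33. The 0.70 is only what the sample can detect; it is not itself a justification.
2. Pre-specify, as a key secondary analysis, a repeated-measures mixed model of FEV1/FVC z-score at 11–14, 16–19 and 24–28 years. Use random effects for participant within pregnancy; fixed effects for steroid exposure, age as a category and their interaction; and one reference equation for all three ages.
3. Base any statement about further deterioration on the steroid-by-age estimate from 16–19 to 24–28 years, with its 95% confidence interval. Do not attach 0.33 to that term. State how many participants have earlier data, and give the expected precision over a range of age-to-age correlations or with the value from the earlier assessments.
4. Say in the text that a difference at 24–28 years alone shows a deficit in level, not further decline.

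The cost is some extra analysis and perhaps recomputing earlier z-scores on one reference set. It needs no extra visits or participants. The longitudinal estimate may be imprecise if many participants lack earlier measurements.

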**Methods:**

A prospective study of participants (aged 24-28) from the United Kingdom Oscillation Study (UKOS) and term born controls. Assessments will involve comprehensive lung function, cardiac ultrasound, exercise assessments, inflammatory cell and biomarker profiling and airway microbiome assessment. The primary outcome is the ratio of forced expiratory volume in 1 s/forced vital capacity (FEV_1_/FVC); to detect a significant difference we will recruit 150 individuals. Statistical analysis will involve mixed effect models with adjustment for imbalances and sensitivity analysis.

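### The primary sample size does not follow from its inputs: a 0.33 difference with SD 1.21 and 90% power needs about 283 per group, and 64 per group gives about 33% power

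*Protocol article*

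**What the plan says.** The Outcome measures section sets the primary comparison: "Our primary outcome is FEV_1_/FVC in extremely prematurely born adults with postnatal corticosteroid exposure versus no postnatal corticosteroid exposure". These are two independent groups.

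The Sample size section then gives every input of the calculation:

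- **Target:** "To detect a clinically significant difference in FEV_1_/FVC of 0.33 between the steroid and non steroid exposed".
- **Origin of the target:** "the difference in the mean FEV_1_/FVC z-score between the results of the 11–14 year olds and 16–19 year olds in the UKOS cohort".
- **Variability:** "with a SD of the FEV_1_/FVC z-score of 1.21".
- **Error rates and result:** "90% power and 5% significance, we will need 64 patients per group", which makes 128 in total, raised to 150 UKOS participants to allow for dropout.

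The same section reports mean z-scores at 16–19 years of −1.83 in the dexamethasone-exposed group and −0.89 in the unexposed group. The abstract repeats the recruitment target: "to detect a significant difference we will recruit 150 individuals".

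**The concern.** A difference of 0.33 against an SD of 1.21 is a standardised effect of 0.33/1.21 = 0.27. An effect that small, at 90% power, needs groups in the hundreds, so 64 per group looked far too few.

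The target also looked misplaced. It is labelled as a difference between exposed and unexposed participants, but its stated source is the change in mean z-score from one age to the next. The only FEV1/FVC gap by steroid exposure in the article is −0.89 − (−1.83) = 0.94, almost three times as large.

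This paragraph is the justification for the study's single primary outcome. The plan calls 0.33 clinically significant and says the study has 90% power to find it. A reader who trusts that claim could take a null result as evidence against a difference of that size.

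**Working it through.** **Inputs (Sample size section).** Difference 0.33, SD 1.21, power 90%, significance 5%, stated result 64 per group. Sidedness is not stated, so two-sided is assumed first. Groups are taken as equal, as the plan does.

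**Formula.** n per group = 2 × (z for significance + z for power)² × (SD/difference)².

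**Control on the plan's other calculation.** For mean pulmonary artery pressure the same section uses a difference of 2.31 mmHg, SD 2.8, 90% power and 0.01 significance:

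2 × (2.576 + 1.282)² × (2.8/2.31)² = 43.7, so 44 per group.

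That is the plan's figure exactly, so the formula is the one that fits the section's other result.

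**Primary outcome.**

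2 × (1.960 + 1.2816)² × (1.21/0.33)² = 282.5, so 283 per group, 566 in total. The t-test version gives 284 per group. The stated 64 is not reproduced; it is 64/283 = 23% of the requirement.

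**Other readings of the same inputs.**

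| Reading | n per group |
|---|---|
| Two-sided 5%, 90% power | 283 |
| One-sided 5%, 90% power | 231 |
| Two-sided 5%, 80% power | 212 |
| One-sided 5%, 80% power | 167 |
| One-sample or paired, two-sided, 90% power | 142 (143 to 144 by t-test) |
| One-sample or paired, one-sided, 80% power | 85 |
| 1.21 read as a variance (SD 1.1) | 234 |
| 0.33 read as a standardised effect | 193 |

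None gives 64. Unequal allocation raises the total (636 at 1:2, about 756 at 1:3).

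**What would give 64 (normal approximation).**

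- Keeping the difference at 0.33, the SD would have to be 0.33/(3.2415 × √(2/64)) = 0.58.
- Keeping the SD at 1.21, the difference would have to be 3.2415 × 1.21 × √(2/64) = 0.69 (0.70 by t-test).
- Keeping both, covariate adjustment would have to remove 1 − 64/283 = 77% of the variance, a correlation of about 0.88.

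**Power with the planned numbers (two-sided t-test, SD 1.21, equal groups).**

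| Per group | Power for 0.33 | Difference detectable with 90% power |
|---|---|---|
| 64 | 33.4% | 0.70 |
| 75 (all 150 evaluable) | 38.2% | 0.64 |

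Even a one-sided test at 64 per group has only about 46% power for 0.33 (normal approximation).

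**Precision.** With 64 per group the 95% confidence interval has a half-width of 1.96 × 1.21 × √(2/64) = 0.42, wider than the 0.33 target.

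**The 0.94 gap.** 2 × (3.2415)² × (1.21/0.94)² = 34.8, so 35 per group would suffice, and 64 per group gives 99% power.

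**The case against.** Nobody can say from the article which number is wrong. The difference or the SD may be mistyped, or an assumption may have been left out. The 33% figure holds only if 0.33 and 1.21 are the intended values. This stands, and it affects the remedy: the four quantities need reconciling, and 0.70 should not be presented as the sponsor's true target. It does not rescue the sentence, which is wrong as printed.

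The covariate adjustment in the Statistical analysis section might reduce the requirement. It would have to explain about 77% of the variance. The sample size claims no such gain, and the section plans adjustment for observed imbalances without citing any gain in precision.

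A past decline may serve as a benchmark for a meaningful difference between groups, and the plan does disclose where 0.33 comes from. That is fair, so the origin of 0.33 is a secondary point: the plan should say that a change over time is being borrowed as a between-group target, and why.

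The 0.94 gap concerns dexamethasone exposure at 16–19 years, and the section does not say whether it is adjusted. The 99% power figure is therefore illustrative only.

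The plan will report estimates with 95% confidence intervals, so a null result near zero would visibly fail to exclude 0.33. This limits the risk of misreading but leaves the false planning claim in place. The abstract states no difference or power and agrees with the 150 elsewhere; it is at most incidental.

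**Conclusion.** The concern holds. The printed inputs require 283 per group (284 by t-test), more than four times the stated 64. With 64 per group the study has about 33% power for the difference it calls clinically significant, so it would miss a true 0.33 about two times in three. The claim of 90% power for the primary outcome is wrong as written.

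This rests on a two-sided test, equal groups, SD 1.21 and no allowance for clustering by multiple births. Unequal exposure groups would lower power further: an assumed split of 40 and 88 gives about 29%. Clustering would generally lower it too.

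The shortfall is against the stated 0.33 target. It does not mean the study is too small for every plausible difference; a gap as large as the 0.94 seen at 16–19 years would very probably be found.

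**What to change.** Reconcile the difference, SD, power and sample size in the Sample size section, or state the assumption that makes 64 correct.

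If the target of 150 stays and the SD is right, one wording would be: with 64 evaluable participants per group, the study has 90% power (two-sided 5%, SD 1.21) for a between-group difference of 0.70 z; the difference observed at 16–19 years was 0.94; power for a difference of 0.33 is about 33%. The sponsor would then need to say why 0.70 is a sensible target, since the article gives it no clinical basis.

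Either drop the statement that the study is powered for 0.33, or present 0.33 openly as a change over time in the cohort. The abstract's sentence on 150 individuals could be aligned with the corrected claim.

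The cost is a text correction with no extra participants, at the price of a less favourable detectable difference. If the sponsor wishes to keep 0.33 with 90% power, the stated inputs would require about 566 evaluable participants.
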